### Additional consent provisions for collection and use of participant data and biological specimens in ancillary studies {26b}

Not applicable.

## Interventions

### Explanation for the choice of comparators {6b}

This is a non-comparative EAP. All patients enrolled in the study will receive tecovirimat according to the Investigator’s Brochure (IB).

### Intervention description {11a}

Patients will be treated as inpatients at participating centres. Tecovirimat is administered by the PI or Co-I in CAR based at the participating district hospital according to the IB.

Tecovirimat should be taken within 30 minutes after a meal ideally of moderate or high fat.

Treatment is given for 14 days following the dosing regimen described in Tables 1 and 2.

**Table 1 pone.0278957.t001:** Dosage for adult patients weighing ≥40kg.

Body weight	Dosage	Number of capsules
40kg to 120kg	600mg twice daily	3 capsules twice daily
≥120kg	600mg three times daily	3 capsules three times daily

**Table 2 pone.0278957.t002:** Dosage for adults weighing <40kg and children.

Body weight	Dosage	Number of capsules
13kg to 24kg	200mg twice daily	1 capsule twice daily
25kg to 39kg	400mg twice daily	2 capsules twice daily
≥40kg	600mg twice daily	3 capsules twice daily

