### Criteria for discontinuing or modifying allocated interventions {11b}

No modifications to treatment administration are permitted under this protocol.

Discontinuation of treatment will only take place on the request of the patient or at the discretion of the PI or Co-I (e.g. as a result of an intolerable adverse event). Discontinuation of treatment will be considered withdrawal from the study and the reason for withdrawal will be recorded on the Case Report Form (CRF).

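### The dose tables give an adult of exactly 120 kg two doses and, unless weight is taken in whole kilograms, leave weights between 24 and 25 kg and between 39 and 40 kg without a row

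*Protocol article*

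**What the plan says.** The Intervention description {11a} says that tecovirimat is given according to the Investigator's Brochure, for 14 days, on the regimen in Tables 1 and 2.

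- Table 1 is headed "Dosage for adult patients weighing ≥40kg". Its rows are "40kg to 120kg 600mg twice daily" and "≥120kg 600mg three times daily".
- Table 2 is headed "Dosage for adults weighing <40kg and children". Its rows are "13kg to 24kg 200mg twice daily", "25kg to 39kg 400mg twice daily" and "≥40kg 600mg twice daily".

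Eligibility criteria {10} admits patients from 13 kg upward with no upper limit. The informed consent section {26a} sets adulthood at 18 years. The article gives no precision for recording weight and no rounding rule.

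**The concern.** A weight-band table should place each eligible weight in exactly one row. These tables fail that test in two ways. The upper limit of Table 1's first row is also the lower limit of its second row. Table 2's rows stop at one whole number and resume at the next, while its title and last row use limits (<40 kg and ≥40 kg) that leave no space between them.

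What is at stake is the dose for a patient at a boundary. The tables are the article's operative dosing statement, every enrolled patient is treated from them, and children are enrolled at weights where both gaps can occur.

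**Working it through.** No sample size, power or error rate is involved, so there is no planned figure to reproduce. The check maps each eligible weight to the rows as printed, separately for adults and children.

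**Daily dose by row** (dose × times per day):
- 13 to 24 kg: 200 × 2 = 400 mg/day
- 25 to 39 kg: 400 × 2 = 800 mg/day
- 40 to 120 kg (Table 1), or ≥40 kg (Table 2): 600 × 2 = 1200 mg/day
- ≥120 kg (Table 1 only): 600 × 3 = 1800 mg/day

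**Mapping.** Weights from 13 to 150 kg were run through the rows in steps of 0.1 kg and of 1 kg. The title of each table decided who belongs to it: adults of 40 kg or more in Table 1; adults under 40 kg and all children in Table 2.

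| Recorded to | Group | Weights with no row | Weights with two rows |
|---|---|---|---|
| 0.1 kg | Adults | 24.1–24.9 and 39.1–39.9 kg | 120.0 kg |
| 0.1 kg | Children | 24.1–24.9 and 39.1–39.9 kg | none |
| 1 kg | Adults | none | 120 kg |
| 1 kg | Children | none | none |

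**Overlap.** At 120 kg an adult matches 1200 and 1800 mg/day, a ratio of 1800/1200 = 1.5. This appears at both recording precisions.

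**Gaps.** These appear only with fractional weights. Take an adult of 39.6 kg: Table 1 starts at 40 kg, so its title excludes the patient. Table 2's title includes the patient, but the second row has ended at 39 kg and the third begins at 40 kg. At 24.6 kg the first row has ended and the second has not begun.

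**What rounding would do.**
- 24.6 kg: cut to 24 kg gives 400 mg/day; rounded to 25 kg gives 800 mg/day. Ratio 800/400 = 2.0.
- 39.6 kg: cut to 39 kg gives 800 mg/day; rounded to 40 kg gives 1200 mg/day. Ratio 1200/800 = 1.5.

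So whole-kilogram recording gives every such patient a row, but which row depends on a convention that the article does not state.

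**The case against.** The strongest defence is that the bands are plainly written in consecutive whole kilograms, and on that scale Table 2 has no gap. That is correct, and it makes the gap part of this point conditional. One can also argue that a patient of 39.5 kg is kept out of the ≥40 kg row, so the 25 to 39 kg row is the evident choice, and likewise the lowest row at 24.5 kg. This is a sensible reading, but it amounts to rounding down, and ordinary rounding to the nearest kilogram would often give the higher dose. The text does not choose between them.

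A second defence is that the Investigator's Brochure governs and may settle every boundary. It is not shown, so that cannot be excluded. The article nevertheless sets out its own tables as the regimen. If the brochure has clean bands, the tables should match them. Neither defence removes the overlap at 120 kg.

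A third is scale: the definite defect is one exact weight, analyses are descriptive, and the dose ratios are only the planned steps between adjacent bands, which any cut-off has. All of this stands. The ratios show how far apart the two candidate doses are, not an error in the results.

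Three stronger readings are tempting and are not supported.

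- A reader might infer that the tables contradict each other at 120 kg and above, because a child stays on two doses a day while an adult has three. The table titles define mutually exclusive groups, so nobody gets two doses or none from this, and the difference may be intended.
- A reader might infer from "No modifications to treatment administration are permitted under this protocol" that the site may not resolve a boundary case. That sentence is in the section on discontinuing or modifying treatment {11b}; it concerns changing a treatment already assigned, not choosing the starting band.
- A reader might infer that completion of treatment or the safety outcomes would be distorted. Weight-band dosing already spans 400 to 1800 mg/day by design, and nothing in the planned descriptive summaries changes.

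**Conclusion.** The point holds in limited form. The overlap at 120 kg in Table 1 is a definite contradiction, with candidate doses of 1200 and 1800 mg/day, and needs no assumption beyond the printed rows. The gaps at 24 to 25 kg and 39 to 40 kg are real as printed, with 2-fold and 1.5-fold differences between the adjoining doses. They leave a patient without a row only if weight is recorded in fractions of a kilogram, and only if no rounding rule exists in documents not shown.

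The article gives no weight distribution, so the number affected cannot be calculated. With one exact weight and two intervals narrower than a kilogram, it is likely to be small. No planned estimate or sample size changes. This is a minor correction, worth making because it concerns a dosing instruction, partly for children.

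**What to change.** Restate the bands so that each eligible weight falls in exactly one row:

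- Adults: 13 to <25 kg, 25 to <40 kg, 40 to <120 kg, ≥120 kg.
- Children: 13 to <25 kg, 25 to <40 kg, ≥40 kg.

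Check each limit against the Investigator's Brochure first, in particular which row should hold exactly 120 kg. The bands above put it in the upper row, keeping the printed ≥ sign; the article cannot settle which dose is right. If the sponsor prefers whole-kilogram bands, it should state the rounding rule beside the tables and still remove the overlap at 120 kg.

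The cost is a wording change to two tables, submitted as an ordinary amendment to the ethics committees. It needs no extra data, visits or staff.

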### Criteria for discontinuing or modifying allocated interventions {11b}

No modifications to treatment administration are permitted under this protocol.

Discontinuation of treatment will only take place on the request of the patient or at the discretion of the PI or Co-I (e.g. as a result of an intolerable adverse event). Discontinuation of treatment will be considered withdrawal from the study and the reason for withdrawal will be recorded on the Case Report Form (CRF).

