### Outcomes {12}

Treatment effects will be evaluated based on clinical, virological and safety outcomes described in Table 3.

**Table 3 pone.0278957.t003:** Outcome measures.

Assessment of…	Outcome measure
**Clinical outcomes**	Time to lesion(s) resolution, defined by: From a start point of date that treatment started. Until an endpoint of up to 14 days since treatment start. Where lesion resolution is the first day on which all lesions are resorbed, scabbed or desquamated and mucosal ulcers healed, and in the absence of any serious complications
	Clinical status defined by: Clinical status on day 14 and day 28 according to an ordinal scale assessed by a physician. The ordinal scale is a) no new or active lesions and no serious complications, b) active lesions and no serious complications, c) serious complication of monkeypox, d) death.
**Virological outcomes**	Virological status defined by Change from baseline in Monkeypox virus DNA levels in throat swabs on days 4, 8, 14 and 28. Change from baseline in Monkeypox virus DNA levels in blood on days 4, 8, 14 and 28. Presence of Monkeypox virus DNA in lesion swabs on days 4, 8, 14 and 28.
**Safety outcomes**	Number and type of Serious Adverse Events (SAEs), Suspected Adverse Reactions (SARS) and Suspected Unexpected Serious Adverse Reactions, (SUSARs) within 28 days of enrolment.

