## Statistical methods

### Statistical methods for analysing outcomes {20a}

Clinical and virological outcomes will be assessed at D14 and D28 for all patients and then at D21 for patients who are still positive at D14. Due to the non-comparative nature of the study and small number of patients anticipated to be enrolled in the study, only descriptive analyses of clinical and virological outcomes will be presented in the final analysis; no inferential statistical testing will be performed to evaluate changes in outcomes.

To describe the cohort, patient demographics will be described in terms of the ratio of males to females in the cohort, and the median age and range in years. The number and percentage of patients with comorbidities at inclusion, including malaria and human immunodeficiency virus, infection will be presented, along with the median interval in days from symptom onset to initiation of treatment.

Signs and symptoms will be reported in terms of the number and percentage of patients presenting with the symptom, which are assessed at each visit and will be reported at baseline and post-baseline timepoint. Signs and symptoms will be reported for all patients both from a pre-defined list included in the CRF and any additional AEs that may have arisen from the point of consent until D28. The signs and symptom reporting will also include the number and percentage of patients with lesions–subcategorised in to active lesions, crusts and resolved lesions–their distribution and number of lesions observed.

Treatment adherence will be reported in terms of the number and percentage of patients who completed a full course of treatment. Non-adherence will be reported in a supplementary narrative explanation.

Patient outcomes will be reported as the number and percentage of participants who meet the clinical criteria described in Table 3 at D14 and D28, along with the number and percentage of participants who tested positive for mpox virus on D4, D8, D14, D21 and D28.

Narrative summaries of SAEs will be presented alongside a tabulated summary of the number and percentage of patients who experience each SAE, for which event names will be MedDRA coded. For each SAE the grade and outcome will be reported.

Full details of the planned analyses can be found in the Statistical Analysis Plan.

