### Methods in analysis to handle protocol non-adherence and any statistical methods to handle missing data {20c}

The reporting of the study results will consist of descriptive statistics, covering patient demographics, signs and symptoms, clinical outcomes, virological outcomes, and treatment data. Missing data will be clearly reported through the use of denominators or narrative explanations of protocol non-adherence.

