### Adverse event reporting and harms {22}

Details of Adverse Events (AEs) and Serious Adverse Events (SAEs) are collected from the point of consent until the Day 28 visit.

AEs and SAEs are defined and reported according to the WHO Collaborative Centre definitions incorporated in to the European Medicines Agency Guideline for Good Clinical Practice E6 [16].

AEs are recorded directly on the standardised paper CRF and transferred on to the RedCap database by the data manager. The data collected for all AEs includes the event name, event grade, start and end dates and outcome.

SAEs require expedited reporting to the Sponsor. SAEs are defined as any untoward medical occurrence that:

results in deathis life-threateningrequires inpatient hospitalisation or prolongation of existing hospitalisationresults in persistent or significant disability/incapacityconsists of a congenital anomaly or birth defect.

Other ‘important medical events’ may also be considered a serious adverse event when, based upon appropriate medical judgement, the event may jeopardise the participant and may require medical or surgical intervention to prevent one of the outcomes listed above.

All SAEs should be reported to the Sponsor and PI on the standardised SAE report form within 24 hours of the site-based programme team becoming aware of the event.

The treating clinician (the PI or Co-I) will provide a causality assessment of the relationship between the event and tecovirimat. The relationship will be evaluated as either: 1) definitely related; 2) probably related; 3) possibly related; 4) unlikely to be related; 5) not related. The Medical Monitor will provide a second causality assessment using the same scale. Events will be considered as “related” to tecovirimat if either causality assessment is returned as “definitely”, “probably”, or “possibly” related. These events will be considered as Serious Adverse Reactions (SARs). Events that are considered to be “unlikely” or “not related” will remain as SAEs.

The Medical Monitor will also assess the expectedness of the event against the Investigator’s Brochure (IB). Related events that are unexpected will be considered SUSARs.

All SAEs must be reported to the ethics committee of the University of Bangui within 72h of the programme team becoming aware of the event.

All SARs must be reported to the Oxford Tropical Medicine Ethics Committee (OxTREC) within 7 working days.

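### Stopping tecovirimat counts as leaving the study, which contradicts the promise of outcome and safety follow-up to Day 28 for all patients

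*Protocol article*

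**What the plan says.** Section {11b} (criteria for discontinuing or modifying interventions) permits no change to treatment administration. Stopping occurs on the patient's request or "at the discretion of the PI or Co-I (e.g. as a result of an intolerable adverse event"). It then rules: "Discontinuation of treatment will be considered withdrawal from the study". The only step that follows is entry of the reason on the CRF.

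Other sections of the protocol article describe follow-up with no exception for patients who stop:

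- Section {20a}: "Clinical and virological outcomes will be assessed at D14 and D28 for all patients". The same section reports how many patients completed the full course and describes non-adherence in a narrative.
- Section {22}: "Details of Adverse Events (AEs) and Serious Adverse Events (SAEs) are collected from the point of consent until the Day 28 visit".
- Section {12}, Table 3: SAEs, SARs and SUSARs are counted "within 28 days of enrolment", and death is a category of clinical status at both D14 and D28.

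On gaps in the data, section {20c} says: "Missing data will be clearly reported through the use of denominators or narrative explanations of protocol non-adherence".

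**The concern.** The protocol gives one status to two different events: stopping the drug and ceasing to be followed. Its own example of stopping is an intolerable adverse event, so the patients affected are especially informative about safety. A site that applies {11b} literally would treat such a patient as withdrawn and could reasonably make no further assessments. A site that applies {20a} and {22} would carry on to Day 28. The document does not say which reading prevails.

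What is at stake is the secondary objective in section {7}, which is to describe clinical, virological and safety outcomes. The background section says that efficacy and safety data for this use are limited. The reported percentages are the whole result here, and the cohort is small: ethics approval covers 100 patients, and section {21b} cites a report on the first 14. One patient lost from 14 is 1/14 = 7.1% of that cohort.

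**Working it through.** There is no planned dropout, power or sample-size figure to reproduce. The check is a reading of the text, followed by an illustration.

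**Step 1: the sections side by side.** Take a patient who stops on Day 5.

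- Under {11b} the patient has left the study on Day 5 with a reason recorded.
- Under {20a} the same patient is assessed at D14 and D28.
- Under {22} and Table 3 the patient's adverse events are collected and counted to Day 28.

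These cannot all apply. Section {18b} does not settle it: it ties the hospital stay to completing treatment and does not mention patients who do not complete.

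**Step 2: which data are exposed.** The adverse event that leads to stopping falls inside the collection window and its reason goes on the CRF, so it is captured. Exposed are later adverse events, SAEs and deaths, the D14 and D28 clinical status, and the remaining scheduled samples.

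**Step 3: effect on reported mortality.** Let p be overall 28-day mortality, s the share who stop, and q the mortality among those who stop. Assume every death among them occurs after stopping and goes unrecorded.

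- Completers as denominator: (p − s·q)/(1 − s)
- All enrolled as denominator, those deaths lost: p − s·q

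Inputs: p = 10%, from the approximate Clade I case fatality in section {6a}. The document gives neither s nor q; both are assumed.

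| s | q | Completers only | All enrolled, deaths lost |
|---|---|---|---|
| 5% | 10% | (0.10 − 0.005)/0.95 = 10.0% | 9.5% |
| 5% | 25% | (0.10 − 0.0125)/0.95 = 9.2% | 8.8% |
| 5% | 50% | (0.10 − 0.025)/0.95 = 7.9% | 7.5% |
| 10% | 10% | (0.10 − 0.01)/0.90 = 10.0% | 9.0% |
| 10% | 25% | (0.10 − 0.025)/0.90 = 8.3% | 7.5% |
| 10% | 50% | (0.10 − 0.05)/0.90 = 5.6% | 5.0% |

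With all enrolled as denominator, any lost death lowers the figure. With completers only, the figure falls below p when q exceeds p and is unchanged when q equals p.

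**Step 4: effect on clinical success.** Assume true D14 success of 80%, 10% stopping, and 50% success among those who stop.

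- Completers only: (0.80 − 0.10 × 0.50)/0.90 = 83.3%, too favourable.
- All enrolled, with unobserved patients not counted as successes: 0.80 − 0.05 = 75.0%, too unfavourable.

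The sign of the error in clinical success therefore turns on the denominator, which {20c} does not specify.

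**The case against.** The strongest reply is that the document never says patients who stop are excluded from analysis or that their data are deleted. Sections {20a} and {22}, read alone, require collection in everyone to Day 28, and the adherence summary keeps non-completers in the report. That stands: loss of data is a risk created by a contradiction, not a stated exclusion.

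A reader might infer that the safety data of patients who stop disappear altogether. They do not, for the reason given in step 2. If the triggering event is serious, it is also reported to the sponsor within 24 hours and assessed by the medical monitor.

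A reader might also infer that patients stop because they are deteriorating, and that clinical outcomes are therefore bound to look too good. Section {11b} does not name deterioration; it could enter only through investigator discretion. Steps 3 and 4 show cases with no bias and with bias in the opposite direction.

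Nor does {20c} say that gaps are handled by shrinking the denominator. It promises denominators or narrative, and the choice of denominator may properly sit in the SAP.

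Finally, the programme's primary objective is access, it has no comparator, and no testing is planned, so no power or decision rule is affected. That limits the consequences but does not remove the conflict. Whatever the SAP says about denominators, it cannot recover assessments, samples or events that were never collected.

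**Conclusion.** The point holds as an internal contradiction with a real risk to data completeness. Section {11b} equates stopping treatment with leaving the study and provides no follow-up off drug; {20a}, {22} and Table 3 require follow-up of all patients to Day 28. Deaths or SAEs missed after stopping would generally understate harm. The direction of bias in clinical success is not determined by the document.

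The size is unknown, because the document gives no stopping rate and no outcome risk after stopping. The 10.0% to 5.6% range for completer-only mortality at 10% stopping rests on assumed values and on the further assumption that all deaths among those who stop go unrecorded. It shows what could happen; it is not a forecast. The correction is cheap and has to be made during data collection.

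**What to change.** Reconcile {11b} with {20a}, {22} and Table 3 by amending {11b} along these lines: discontinuation of tecovirimat is recorded separately from withdrawal of consent for follow-up; patients who stop early continue scheduled assessments, samples and AE/SAE collection to Day 28 unless they withdraw consent for follow-up.

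State how these patients are counted:

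- Report D14 and D28 clinical and virological outcomes for all PCR-confirmed patients who started treatment.
- Report safety for everyone who received at least one dose. Section {10} lets presumptive cases enrol before the PCR result and exit if negative, so show dosed patients who later test negative separately, for the period observed.

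The cost is a few additional follow-up assessments, and separate recording of date and reason for stopping the drug and for leaving the study. The CRF is not shown, so whether new fields are needed cannot be checked. The change concerns data collection and reporting only; no clinical stopping rule is proposed.

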### Strategies to improve adherence to interventions {11c}

Treatment is administered by the PI or Co-I to ensure adherence.

Drug dispensing is recorded on a drug accountability log on which any unused capsules are also recorded.

